### Process evaluation: non-response, adherence and cost-effectiveness

In addition to the effect evaluation a process evaluation will be carried out.

A non-response analysis will be conducted to determine possible selection bias. In the non-response analysis the following characteristics of (non)-participating children and their parents will be considered: ethnicity of the parents and children, educational level of the parents, household composition, an indication of the levels of the four target behaviours reported by the parents, and self-reported BMI of the parents and their children. For adherence to the prevention protocol the following variables are registered: classification of the children by the YHC professionals to the correct weight status according to the international age and gender specific cut-off points of BMI, the number of sessions the parents of overweight children attend, and the intensity of the sessions (i.e. did the parents complete energy intake and/or expenditure diaries, draw up a family-oriented action plan with the YHC professional, etc.). Adherence of both the YHC professionals and parents to the different elements of the prevention protocol will be analysed in relation to changes in BMI, waist circumference, and lifestyle of the children by multiple linear or logistic regression analysis (depending on the type of outcome variable). Analysis of these variables may indicate which elements of the prevention protocol work (or do not work), and for whom. In addition, satisfaction with the protocol of parents and YHC professionals will also be assessed. Finally, a cost-effectiveness analysis will be performed using a societal perspective, including program and parents costs.

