## Methods and design

### Study design

This cluster randomised controlled trial is conducted in the Netherlands among children aged about 5 years and their parents, who are invited by the MHSs for a regular preventive health check. The YHC teams that perform the check consist of a physician, a nurse and an assistant; they form the unit of randomisation. The randomisation code was developed using a computer random number generator in SPSS to select random permuted blocks (specified allocation ratio 1:1). The block lengths were 4 or 6, depending on the number of YHC teams that participate per MHS. Within the MHSs an even number of YHC teams were randomly allocated to the two study arms: an intervention and a control group. The teams in the intervention group offer the prevention protocol to parents of overweight children, and in the control group the teams offer usual care to these parents. The effects of the prevention protocol will be evaluated after two years of follow-up by comparing the outcomes of BMI and waist circumference of the overweight children with those of the children in the control group, taking into account the baseline values of these measures [20,27]. Data collection started in September 2007 and will continue until August 2010. The Medical Ethics Committee of the Erasmus Medical Centre Rotterdam approved the study protocol (reference number MEC-2007-163).

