### Sample size

Sample size was calculated taking into account the intra-cluster correlation coefficient (ρ = 0.1), the number of clusters (44), the expected prevalence of overweight children in the study population, the standard deviation (SD), expected effect (a difference in mean), and the power of the study (80%). With a participation of 50%, an expected prevalence of overweight children of 9% and a loss-to-follow-up of 30%, at least 1,1301 children (and their parents) should be invited by the YHC teams to participate in the study to have a final sample of about 356 overweight children (178 in both the intervention and control group). Assuming a SD of BMI to be 1.0 kg/m^2 ^[36], a difference in mean BMI of 0.35 kg/m^2 ^between the children in the intervention group and the children in the control group can be established under the assumptions mentioned above. Assuming an SD of the average number of hours per day of watching TV, video, DVD and playing computer games combined to be 60 minutes per day [36,41,42], a difference of 20 minutes per day can be established.

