### Statistical analysis

The aim of the study is to assess the effectiveness of the prevention protocol among children with overweight. An intention-to-treat analysis will be applied [43]. Multi-level analyses will be applied because of the three-level structure of the study, i.e. correlation of the repeated observations within a participant and the correlation of the observations of participants within a YHC team [26,44]. Linear multilevel analysis will be applied for continuous outcome variables and logistic multilevel analysis for dichotomous outcome variables [44]. Biometric and behavioural outcomes of the children at age 7 years will be analysed with independent variables: intervention or control group, gender, age, socio-economic status, ethnicity, weight of the parents, and baseline levels of the outcome variables. Interaction effects of gender, social disadvantage and ethnic background with the effect of the prevention protocol will be explored.

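### The adherence analysis names ordinary regression with no team level, so tests on adherence variables that differ between teams would be moderately too liberal

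*Protocol article*

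**What the plan says.** Three sections of the protocol article bear on this.

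- **Process evaluation.** Adherence of both professionals and parents is to be related to changes in BMI, waist circumference and "lifestyle of the children by multiple linear or logistic regression analysis (depending on the type of outcome variable". The section then says: "Analysis of these variables may indicate which elements of the prevention protocol work (or do not work), and for whom". The registered variables are whether the child's weight status was classified correctly, how many sessions the parents came to, and how intensive those sessions were (diaries completed, action plan made).
- **Statistical analysis.** The effect analysis is multilevel, linear or logistic. One stated reason is "the correlation of the observations of participants within a YHC team". Baseline levels of the outcomes are among the independent variables.
- **Sample size.** The calculation rests on an "intra-cluster correlation coefficient (ρ = 0.1), the number of clusters (44" teams), and aims for "a final sample of about 356 overweight children (178 in both the intervention and control group").

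The Discussion returns to the adherence results. Without the hedge used in the process section, it expects the process data to shed light on which parts of the protocol are effective.

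**The concern.** For the same outcomes in children of the same teams, the plan uses multilevel models in one section and plain regression in the next. The wording does not expressly exclude a team effect. But where the multilevel form is named for one analysis and not for the other, single-level regression is the natural reading. This is a stated method that conflicts with the plan's own reasoning, rather than a detail left out.

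It matters most for what professionals do. Most elements in the Appendix are actions of the YHC professional, and one team delivers them to all its children, so some between-team variation in adherence is a reasonable expectation. Where both predictor and outcome are correlated within teams, ordinary regression overstates precision.

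Two further features affect how the results can be read:

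- The outcomes are described as changes, with no baseline adjustment named, in children selected for high BMI. If adherence were related to baseline BMI, regression to the mean would enter the comparison.
- Parents decide whether to attend and to keep diaries, so adherence is not randomised. An association does not show that an element works.

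At stake is a list of apparently effective elements that is longer, or held with more confidence, than the data justify.

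**Working it through.** **Inputs from the documents**

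- Outcome ICC 0.1, 44 teams, 356 children analysed (178 per arm), participation 50%, prevalence 9%, loss to follow-up 30%, SD 1.0 kg/m², detectable difference 0.35 kg/m², power 80% (Sample size).
- 1:1 allocation (Study design), taken to give 22 intervention teams.

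**Assumptions**

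- The ICC of the adherence variable (ICC_x) is not given, so it is varied from 0 to 1.
- Teams are of equal size.
- The planning ICC applies to the adherence outcomes. The documents do not say this, so lower values are shown too.

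**The plan's own figures first**

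Invited: 356 / (0.50 × 0.09 × 0.70) = 356 / 0.0315 = 11,301.6, which agrees with the printed figure read as 11,301.

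Mean team size: m = 356 / 44 = 8.09. Design effect for a team-level comparison: 1 + (8.09 − 1) × 0.1 = 1.709.

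Detectable BMI difference at 80% power: (z for alpha + 0.842) × √(2 × 1.709 / 178). This is 0.345 kg/m² with one-sided 5% and 0.388 kg/m² with two-sided 5%. The article states neither alpha nor sidedness. The 0.35 is reproduced at ICC 0.1 on the one-sided reading. Nothing below depends on this.

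The plan states no figure for the adherence analysis itself.

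**Effect of ignoring team**

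The variance of a regression slope is understated by a factor of about

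DE = 1 + (m − 1) × ICC_y × ICC_x

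and the true type I error of a nominal two-sided 5% test is 2 × [1 − Φ(1.96 / √DE)]. With m = 8.09 and ICC_y = 0.1:

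| ICC_x | DE | True SE / naive SE | Type I error, formula | Type I error, simulated |
|---|---|---|---|---|
| 0 | 1.000 | 1.00 | 5.0% | 4.9% |
| 0.1 | 1.071 | 1.03 | 5.8% | 5.9% |
| 0.3 | 1.213 | 1.10 | 7.5% | 7.4% |
| 0.5 | 1.355 | 1.16 | 9.2% | 8.9% |
| 1 | 1.709 | 1.31 | 13.4% | 13.1% |

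The simulation used 22 teams of 8 children, a continuous outcome and 20,000 replicates.

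In the last row the naive standard error is 1 / 1.307 = 0.765 of the true one, about 24% too small. The 178 children carry the information of 178 / 1.709 = 104 independent ones, and a naive p of 0.01 corresponds to about 0.049.

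**Sensitivity to the outcome ICC, with ICC_x = 1**

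- ICC_y = 0.05: DE = 1.355, type I error 9.2%.
- ICC_y = 0.02: DE = 1.142, type I error 6.7%.

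**The case against.** The strongest reply is that this is a hedged, secondary analysis in a condensed article, and that the large figure belongs to a variable the plan does not list. Each registered adherence variable is recorded per child or per family, and none is by definition constant within a team. No adherence ICC is given, and 0.1 is a planning value not stated to apply to these outcomes. All of that stands, and it is why the result is a range with 13% as its upper end.

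A reader might infer more than the documents support:

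- *That all p-values are far too small.* With about 8 children per team the inflation is moderate at worst. It is slight or absent for variables that vary mainly within teams, as parents' attendance or diaries may.
- *That ignoring clustering means the analysis cannot show which elements work.* Clustering affects precision and does not by itself bias the associations. What limits that conclusion is that adherence is not randomised.
- *That the process section makes a firm causal claim.* Its own wording is tentative; only the Discussion is firmer, and neither sets a decision rule.
- *That an unadjusted change score is fixed.* The covariates of the regression are not listed, and nothing shows that heavier children's parents attend more. The regression-to-the-mean point is therefore conditional.

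The appeal to condensation does not dispose of the core. The article names a method here, and it differs from the one it justifies a section earlier.

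**Conclusion.** The point holds in moderate form. As written, the adherence regressions ignore a correlation that the plan recognises for the same outcomes, and standard errors would be too small for adherence variables that vary between teams. At ICC 0.1 and 8.09 children per team, true type I error is about 6% to 9% for adherence ICCs of 0.1 to 0.5, and about 13% in the limiting case of a wholly team-level variable. A smaller outcome ICC lowers these figures. They rest on the assumed adherence ICC, equal team sizes, 22 intervention teams and the planning ICC carrying over.

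The primary intention-to-treat analysis is untouched. Separately, because adherence is not randomised, wording about elements that work goes further than this analysis can support, however clustering is handled.

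**What to change.** In the process-evaluation section, replace the regression sentence with text such as:

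> Associations between adherence variables and BMI, waist circumference and behaviour at follow-up will be estimated with linear or logistic multilevel models that include a random intercept for YHC team and the baseline value of the outcome as covariate.

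Team-robust standard errors would be an acceptable alternative to the random intercept. Using the follow-up value with baseline as covariate follows the Statistical analysis section and deals with the change-score question.

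In the process-evaluation section and the Discussion, describe the results as elements associated with outcome rather than elements that work or are effective.

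Fixed effects for Municipal Health Service are not needed for this correction. The main model as described lists none, and with 9 services and about 22 intervention teams they would use up much of the between-team information.

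The cost is a change of wording and model specification, with no new data. Intervals for the adherence results become somewhat wider. At the planning ICC the standard errors grow by about 3% for an adherence ICC of 0.1, and by about 31% in the wholly team-level case.

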### Intervention

The prevention protocol (see appendix) is based on theories and models of behavioural change, i.e. the ASE model, a theoretical model of exercise habit formation, the Precaution Adoption Process Model, the Elaboration Likelihood Model, the stages of change model, and motivational interviewing techniques [29-34]. During the regular preventive health check, when a child in the intervention group with overweight is detected, the parents are offered up to three additional structured lifestyle counselling sessions to promote overweight-preventing behaviours. Prior to the start of the study, the YHC professionals in the intervention group received training in a non-directing guiding style as part of the prevention protocol [35]. The YHC professionals assess whether the parents are motivated to participate in this counselling, and will make use of a motivational interview approach if needed [35]. The three additional structured lifestyle counselling sessions are offered to parents with intervals of 1, 3 and 6 months after the regular preventive health check. The content of each visit depends on the stage of behavioural change that the parents are in [33]. The purpose of the sessions is to make parents aware of the overweight of their child, to provide information about overweight and its consequences, and to motivate the parents for and assist them in behavioural change. Materials that are used during the sessions are: a form for the YHC professional to assess the behaviours that should be targeted within the family, and diaries on energy intake and expenditure to be completed by the parents. Table 1 shows the guidelines for the four target behaviours for children at the age of about 5 years. The YHC professional and the parents together draw up a family-oriented action plan aiming at the promotion of physical activity and outdoor playing time, having family breakfast daily, consuming less sweet drinks and/or limiting watching television/playing computer games (Table 2) [25]. A pilot study has established the feasibility and acceptability of the prevention protocol [36].

**Table 1 T1:** Guidelines used during counselling sessions regarding the four target behaviours for children aged 5 years.

**Behaviour**	**Guideline**
Being physical active	- At least 1 hour each day
	- Moderate intensity (outdoor playing, walking, cycling or doing sport)
Having breakfast	- Daily
	- In the family setting

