## Discussion

This study presents the design of a cluster randomised controlled trial on the prevention of overweight and obesity in children. The study evaluates a protocol that is proposed for application in the YHC setting for the prevention of overweight and obesity in children.

It is hypothesised that, after two years of follow-up, overweight children in the intervention group will have less BMI and waist circumference, spend more time being physically active, more frequently have family breakfast on a daily basis, consume less sweet beverages, and spend less time watching television/playing computer games compared to overweight children in the control group. Differences between subgroups (ethnicity and socio-economic status) regarding the effects of the prevention protocol, and determinants of overweight and obesity, will be described. Several process variables will be registered to measure whether differences exist in subgroups of adherence to the prevention protocol, concerning the positive effects on BMI, waist circumference and lifestyle. This will also provide insight into the effective elements of the prevention protocol.

Strengths of the study are the size of the study (44 YHC teams), the random controlled design, and the regular preventive health check of the MHSs which more than 95% of all invited parents and their children attend [45]. Children receive a YHC check-up at set ages, which offers optimal opportunity to provide tailored prevention. The follow-up at 12 and 24 months allow to investigate the long-term effects of the prevention protocol. Regarding the generalisability of the study results, a first strength is that it is a controlled study conducted in the practice setting. The intervention is applicable in the daily practice of the YHC professionals, which will facilitate implementation of the prevention protocol if it is found to be effective. A second strength regarding generalisability is that the participating YHC teams cover both urban and rural areas. A limitation of the study is that the behaviour of the children and their parents is based on self-reports by the parents.

In conclusion, this study evaluates a protocol for the prevention of overweight and obesity in children. The results of this study will provide insight into the effectiveness of the prevention protocol used in Youth Health Care, and in the determinants of overweight and obesity of children aged 5 to 7 years.

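### Relating sessions attended, diaries and action plans to BMI change cannot show which elements work, because uptake is not randomised and plausibly follows parental motivation

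*Protocol article*

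**What the plan says.** All locations are in the protocol article.

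- **What is randomised** (Study design): YHC teams, to the whole prevention protocol or to usual care. "The teams in the intervention group offer the prevention protocol to parents of overweight children".
- **How families come to receive elements** (Intervention): parents are offered up to three sessions. "The YHC professionals assess whether the parents are motivated to participate in this counselling", with motivational interviewing where needed. "The content of each visit depends on the stage of behavioural change that the parents are in".
- **Adherence variables** (Process evaluation): correct classification of the child's weight status by the professional; "the number of sessions the parents of overweight children attend"; and session intensity, for example "did the parents complete energy intake and/or expenditure diaries, draw up a family-oriented action plan with the YHC professional, etc".
- **Analysis** (Process evaluation): adherence of professionals and parents is related to changes in BMI, waist circumference and lifestyle "by multiple linear or logistic regression analysis (depending on the type of outcome variable").
- **Inference**: "Analysis of these variables may indicate which elements of the prevention protocol work (or do not work), and for whom" (Process evaluation), and then in the Discussion: "This will also provide insight into the effective elements of the prevention protocol".

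The only limitation named in the Discussion is parental self-report of behaviour. Neither section says that the adherence comparison is non-randomised.

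**The concern.** The stated inference is causal, namely which parts of the protocol have an effect, but the design varies none of those parts. Sessions, diaries and action plans are elements of the intervention, so the comparison is made among intervention families who took up more or less of it. A motivated family is more likely to attend, keep a diary and agree a plan, and could plausibly change more without any of these. Parents' readiness to change also shapes what a session contains. Motivation is thus a plausible common cause of exposure and outcome.

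According to the Background, the Municipal Health Services are already preparing to implement this protocol. A statement that certain elements are effective, or are not, could shape what is rolled out while reflecting who attended.

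**Working it through.** **1. Which comparison randomisation protects.** The randomised contrast is offer against no offer, by team. The process regression contrasts levels of uptake within the arm that received the offer. Parental uptake of sessions, diaries and plans is not allocated, so randomisation gives that contrast no protection. Correct classification is an act of the professional and is not chosen by parents.

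**2. The plan's own figures.** This point disputes none of them. The final sample reproduces: reading the printed number invited as 11,301, 11,301 × 0.50 × 0.09 × 0.70 = 355.98, the stated 356 or 178 per arm. About 178 intervention children would therefore enter the adherence regressions. The planned SD of BMI is 1.0 kg/m² and the planned difference between arms is 0.35 kg/m².

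**3. Size of the spurious association (assumed correlations).** Suppose sessions have no true effect.

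- Induced correlation = r(motivation, sessions) × r(motivation, outcome).
- Slope per session = induced correlation × SD(outcome) / SD(sessions).
- SD(outcome) is assumed to be 1.0, borrowing the plan's SD of BMI.
- SD(sessions) is √1.25 = 1.118, assuming 0, 1, 2 and 3 sessions equally likely.
- Three-versus-none difference = 3 × slope.

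| r(motivation, sessions) | r(motivation, outcome) | Product | 3 versus 0 sessions, kg/m² |
|---|---|---|---|
| 0.2 | 0.2 | 0.04 | 0.04 / 1.118 × 3 = 0.11 |
| 0.3 | 0.3 | 0.09 | 0.09 / 1.118 × 3 = 0.24 |
| 0.5 | 0.3 | 0.15 | 0.15 / 1.118 × 3 = 0.40 |

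**4. Does handling clustering help?** A simulation used 178 children in 22 teams, ICC 0.1 and total SD 1.0, with the true effect of every session and of the diary set to zero. Motivation drove both uptake and BMI. The uptake model and motivation effects are assumptions and differ from those in step 3. Sessions and diary were fitted together.

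| BMI reduction per SD of motivation, kg/m² | Spurious 3 versus 0 difference, kg/m² | False positives for sessions, ordinary errors | False positives, cluster-robust errors |
|---|---|---|---|
| 0 | −0.01 | 5% | 5% |
| 0.2 | −0.32 | 26% | 26% |
| 0.3 | −0.48 | 56% | 53% |
| 0.5 | −0.83 | 96% | 95% |

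The cluster correction changes the standard error and leaves the biased coefficient as it is.

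**5. Does adjustment help?** With a motivation effect of 0.3, adding a proxy that captures 30% of the variance of motivation reduces the spurious difference from −0.48 to −0.39 (37% false positives). A proxy capturing 60% reduces it to −0.26 (19% false positives). Adjustment is worthwhile but does not remove the problem.

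**The case against.** The strongest reply is that this is a secondary process analysis, described as additional to the effect evaluation. None of the study hypotheses concerns elements, the Process evaluation sentence is hedged, and no rule for keeping or dropping elements depends on the result. All of that is true and limits the weight of the point. It does not rescue the inference: the hedge is gone in the Discussion, and neither section warns that uptake is self-selected.

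A second reply is that multiple regression leaves room for covariates, that the effect analysis already uses baseline levels, and that a condensed article need not list every covariate. That stands. The missing list is not the defect; the stated conclusion is, and step 5 shows that imperfect adjustment leaves bias.

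A third reply is that the magnitudes rest on assumed correlations, and that a three-versus-none contrast is not the same quantity as the 0.35 kg/m² between arms. Both are right, so 0.35 serves only as a sense of scale. The direction is also open: families whose child is already improving may have less reason to return, which would work the other way.

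Several stronger readings go beyond the text:

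- *Professionals withhold sessions from unmotivated parents.* The Intervention section and the Appendix describe an offer, an assessment of motivation and motivational interviewing where needed. Neither says that the offer is withdrawn.
- *There is no concurrent comparison.* Low attenders in the same arm are one; they are just not a randomised one.
- *Regression to the mean biases the result.* It affects high and low attenders alike unless baseline BMI differs with adherence, which the article does not show.
- *Every adherence variable is affected.* Correct classification is not selected by parents.

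**Conclusion.** The point holds for sessions attended, diaries and action plans. Regressing outcome on these variables estimates a mixture of any element effect and the characteristics of families who take elements up, with or without a team level in the model. It cannot support a statement about which elements work.

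The illustrative size is about 0.11 to 0.40 kg/m² between three sessions and none when the true effect is zero. This rests on assumed correlations of 0.2 to 0.5 (motivation with sessions) and 0.2 to 0.3 (motivation with outcome), an even spread of sessions and an outcome SD of 1.0. The simulation, under other assumptions, gives larger values. Neither range is an estimate for this trial, and the net sign is not known.

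A reader might infer that the trial's main conclusion is at risk. It is not: the effect analysis is by intention to treat, compares randomised arms and does not use adherence.

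**What to change.** 1. **Process evaluation, model.** Analyse the follow-up outcome adjusted for its baseline value, the covariates listed under Statistical analysis, and the baseline parental attitudes and behaviours already collected (Study procedure; Secondary outcomes). Add motivation or stage of change if it is recorded. The article says motivation is assessed but does not list it among the registered variables.
2. **Process evaluation and Discussion, wording.** Replace the claims about which elements work or are effective with a statement that these are exploratory, non-randomised associations between adherence and outcome within the intervention arm.

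The cost is specification and wording, with no new data unless motivation is to be captured where it is not now recorded. The process conclusion becomes softer, and residual confounding remains and should be acknowledged.

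A complier average effect using the randomised arm is optional. It addresses the effect of attending at all and does not answer the element question. It also assumes that the offer acts through the sessions, which is doubtful because motivational interviewing may already take place at the health check.
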